#### 5.3.1.9 Clinical (symptoms) monitoring and referral in case of symptoms or complaints

Study patients will receive clinical (symptoms) monitoring in line with South African NDoH guidelines, as described above (“5.2.3 Clinical assessment”). All patients with a last recorded CD4 count below 200 cells/mm^3 will be monitored by a physician initially and by **the research nurse or clinician** at each subsequent study visit, while all patients with CD4 counts above 200 cells/mm^3 will be monitored by **the research nurse** at each study visit. If symptoms are detected by **the research nurse** the patient will be referred to **the research clinician**, who will document symptoms and will perform a physical exam.

If any medical conditions requiring additional treatment are detected at entry into the study or during follow-up contact moments, participants in both control and intervention arms will be attended to and offered referral to a health care provider of their choice.

### 5.4 Laboratory procedures and storage of blood

A full overview of study blood draws and subsequent sample storage per visit is shown in table 4.

Laboratory tests and procedures (both standard of care and additional measurements in study subjects) will be performed at the on-site Toga laboratories facility (accreditation by the South African National Accreditation System (SANAS)). Genotypic drug resistance testing will be performed by the WHO reference laboratory. All laboratory procedures are described in a Laboratory Manual.

Informed consent will be obtained for storage of samples. In case additional research questions are formulated on the stored plasma samples, the Ethics Committee will be asked for additional approval.

### 5.5 Withdrawal of individual participants

Participants will be informed that they can leave the study at any time for any reason if they wish to do so without any consequences. When a participant decides to leave the study, he/she will be asked for written permission if he/she, or a contact person, can still be contacted in order to gather morbidity/mortality follow up data.

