#### 5.1.2 Control arm follow-up – standard of care HIV treatment monitoring

300 patients randomly assigned to this arm will be monitored in full concordance with current South African NDoH guidelines in use at the study site. Viral load measurements will be performed at month 12 and 24 after start of ART (for newly initiated patients) or at month 12 and 24 after the last VL measurement (patients already on ART). If a VL >1000 copies/ml is detected, the patient is called back for counselling for therapy adherence and repeat VL measurement, 2 months after the initial VL measurement. If the repeat VL measurement is >1000 copies/ml after adherence counselling, this is taken to be indicative of therapy failure due to development of drug resistance and a switch to second line therapy is made, together with intensified adherence counselling, without verifying the cause of virological failure by

performing DLM or drug resistance testing. If VL drops to <1000 copies/ml after adherence counselling, the first line treatment is maintained. For a full overview of study visits and clinical algorithms in the control arm, see Figure 1: ITREMA study flowchart.

Sample collection in the control arm consists of storage of EDTA-derived plasma and a DBS at study baseline and at the subsequent study visits at month 3, 6, 9, 12, 15, 18, 21 and 24 of ART, as well as during any additional study follow-up visits in case of a VL >1000 copies/ml. Blood draws at baseline, month 3, 6, 12 and 24 after start of ART, and in case of follow-up after a VL >1000 copies/ml coincide with blood draws performed as part of standard of care. The following measurements will be performed on stored samples:

- An additional CD4 measurement at study month 6, in order to assess eligibility for randomisation and rate of CD4-count recovery.
- Retrospective VL testing on stored EDTA-derived plasma in case of clinical therapy failure, in order to retrospectively examine the duration of viremia.
- Retrospective drug resistance testing on stored DBS in case of clinical therapy failure to examine the accumulation of resistance mutations over time.
- Screening for transmitted drug resistance by drug resistance testing on stored DBS obtained as at baseline, prior to start of ART.

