### 6.7.3 Sample size calculation

Sample size calculation is based on power analyses using selection of resistance as the primary study outcome. The first outcome used for power calculation is the selection of non-polymorphic K65R drug resistance related mutation in HIV reverse transcriptase that is selected by currently used first line therapy at any time during study follow-up. Previously observed prevalence rates of the K65R mutation in HIV-1 subtype C infected patients experiencing therapy failure of a first-line regimen are 70% in LMIC and 17% in developed settings. Using a  $1-\alpha$  of 0.9 and a  $\beta$  of 0.05, the inclusion of 14 cases of failure per arm is needed. Cumulative virological failure (VL >1000 copies/ml) is anticipated to occur in 15% of patients at 12 months after initiation of ART and at 20% at 18 months. Taking into account a loss to follow-up of 10% per year and 20% failure rate, 83 patients are needed per study arm

to detect differences in resistance development as described in literature.

The study is also powered to detect the expected differences in selection of multiple resistance mutations in both arms at month 18 after therapy initiation, derived from a pilot study we performed at Ndlovu Medical Centre. In this study we saw an increase of 2.8 to 4.3 mutations per additional 6-12 months of prolonged therapy. This difference can be detected with 10 patients with therapy failure (59 patients per study arm at an expected failure rate of 20% and 10% loss to follow-up a year).

The third outcome used for power calculation is based on a cross-sectional analysis of a detectable VL >1000 copies/ml at the end of the trial (study month 24). The number of patients with a VL test result above 1000 copies/mL is estimated to be 15% in the control arm and 5% in the intervention arm. Taking into account a loss to follow-up of 10% a year, initial inclusion of 216 patients per arm is required to detect the anticipated difference.

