#### 7.2.3 Informed consent

The informed consent procedure will be performed by a research health care worker, in the subjects’ home language if necessary. The participant information sheet and informed consent form will be in English. Risks and benefits of study participation will be discussed and all questions will be answered. Written informed consent will be obtained for the study. Patients can give informed consent by signature, thumbprint or ID-mark. In case of patients that are unable to read or write, the health care worker performing the informed consent procedure and an impartial witness will co-sign the consent form with approval of the consenting participant.

Participants may refuse to participate in the study or may withdraw consent at any time and this will not affect their routine clinical care. The participant will receive a copy of the informed consent for their records. Another copy of the informed consent will be filed in the patient's record. Patients will also receive a contact number at which they can contact the study clinician in case of queries or other events.

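### Permission sought at withdrawal covers morbidity and mortality only, so routine month-24 viral loads of withdrawn patients still in care are not provided for

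*Protocol*

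**What the plan says.** Protocol section 5.5 lets participants leave at any time and states what is then sought: the participant is "asked for written permission if he/she, or a contact person, can still be contacted in order to gather morbidity/mortality follow up data". It mentions neither VL, nor treatment switches, nor the clinic record.

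Section 3.2.1 makes morbidity and mortality part of a secondary objective, and section 6.1 lists them as clinical outcomes, apart from the virological ones.

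Section 6.7.3 uses three outcomes for power. It opens with "Sample size calculation is based on power analyses using selection of resistance as the primary study outcome". The third outcome is a "cross-sectional analysis of a detectable VL >1000 copies/ml at the end of the trial (study month 24"), with the proportion "estimated to be 15% in the control arm and 5% in the intervention arm". For this outcome it says: "Taking into account a loss to follow-up of 10% a year, initial inclusion of 216 patients per arm is required".

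On routine care, section 7.2.3 says that participants "may withdraw consent at any time and this will not affect their routine clinical care". Section 5.1.2 schedules VL at months 12 and 24 in line with national guidelines. It lists "Blood draws at baseline, month 3, 6, 12 and 24 after start of ART" among the draws that coincide with standard of care, and section 5.1.3 repeats that sentence. Section 5.4 places standard-of-care and study tests in the same on-site laboratory.

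**The concern.** The follow-up sought after withdrawal serves a secondary objective and leaves out the type of data behind the powered outcome with the largest sample size. For a withdrawn patient who remains at this clinic, the month-24 VL would normally be measured anyway, and a switch to second-line therapy would normally be in the record. Following section 5.5 as written, the trial would not ask for either.

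Allocation is open-label, so the decision to leave may depend on the arm and on adherence, and adherence is closely tied to VL. A month-24 comparison restricted to those who stay could then differ from the comparison in all randomised patients, for want of results the clinic may already hold.

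A later analysis plan cannot repair this. It can say how missing results are handled, but it cannot supply results that nobody asked permission to use.

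**Working it through.** **1. Reproduce the stated sample size.** Inputs from section 6.7.3: 15% v 5%, loss of 10% a year. From section 4.1: 18 months after randomisation, so loss = 1.5 × 10% = 15%. Section 6.7.3 gives no error rates for this outcome, so two-sided alpha 0.05 and power 0.90 are assumed.

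- n = (1.960 + 1.282)² × (0.15 × 0.85 + 0.05 × 0.95) / 0.10² = 10.51 × 0.175 / 0.01 = 183.9 per arm.
- Inflated for loss: 183.9 / 0.85 = 216.3, which matches the stated 216.
- The same 15% reproduces the other two figures: 14 / 0.20 / 0.85 = 82.4 (stated 83) and 10 / 0.20 / 0.85 = 58.8 (stated 59).

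The month-24 VL outcome therefore needs the most patients of the three, and attrition is already allowed for.

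**2. Is power affected?** Power = Φ{[0.10 × √n − 1.960 × √(2 × 0.10 × 0.90)] / √0.175}, where n is the number analysed per arm.

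| Share of lost results recovered | 300 per arm: n, power | 216 per arm: n, power |
|---|---|---|
| none | 255, 96.6% | 183.6, 89.5% |
| half | 277.5, 97.7% | 199.8, 91.8% |
| all | 300, 98.4% | 216, 93.6% |

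At the planned 300 per arm the gain is at most 1.8 points, and less if only withdrawals are recovered.

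**3. How large could the bias be?** Planned loss is 0.15 × 300 = 45 per arm. The protocol does not say how much of this is withdrawal. *Assumptions, none from the protocol:* withdrawals are 25% to 50% of the loss (11 to 23 per arm), 40% of withdrawn patients are viraemic at month 24, and everyone else, including the other lost patients, has the planned 15% or 5%.

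Risk per arm = [(300 − w) × p + w × 0.40] / 300, with w the number withdrawn.

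| Withdrawn, control v intervention | Control | Intervention | Risk difference | Risk ratio |
|---|---|---|---|---|
| none (planned) | 15.0% | 5.0% | 10.0 points | 3.0 |
| 11 v 11 | 47.75/300 = 15.9% | 18.85/300 = 6.3% | 9.6 points | 2.5 |
| 11 v 23 | 47.75/300 = 15.9% | 23.05/300 = 7.7% | 8.2 points | 2.1 |
| 23 v 11 | 50.75/300 = 16.9% | 18.85/300 = 6.3% | 10.6 points | 2.7 |

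The risk difference can move either way. The risk ratio falls in all three scenarios. None reverses the direction of effect.

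**4. Compare with the lost-to-follow-up procedure.** For participants who are lost and consent, section 5.3.1.8 adds a home visit, an in-depth interview and a dried blood spot. For participants who withdraw but may still attend the clinic every month, section 5.5 seeks only morbidity and mortality by contact. The group that is easier to reach has the narrower virological follow-up.

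**The case against.** Several objections have force.

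- *A reader might infer that routine results are barred from use.* Section 5.5 does not say so. It asks for permission to contact and is silent on records. The consent pages are not available here and may already allow it. What stands is that the available text does not provide for it.
- *A reader might take VL to be the outcome that drives the trial.* Section 6.7.3 names resistance selection as primary and lists VL third. Month-24 VL is not named in the primary objective (section 3.1) or in the outcome list of section 6.1. Standard care does no resistance testing (section 5.1.2), so the fix recovers no resistance data. A switch date alone does not show whether a switch was unnecessary.
- *A reader might infer unequal burden from six scheduled VLs against two.* The protocol does not support this. Both arms have three-monthly visits (section 4.1), Table 4 gives one set of blood volumes, and visits and call-backs in both arms coincide with medication collection (section 5.1.1). Only the number of call-backs after a raised VL can differ. The case for informative withdrawal rests on open-label allocation and the link between adherence and leaving.
- *Continued care at this clinic is assumed.* Section 7.2.3 says that routine care is unaffected, not that the patient stays or attends for the month-24 test.
- *Analysis in the randomised arm can be left to the statistical analysis plan.* That is fair for the analysis rule, but not for the permission, which must be sought when the patient leaves.

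**Conclusion.** The point holds as a gap in provision. Section 5.5 seeks contact for morbidity and mortality only. The month-24 VL, one of three powered outcomes and the one with the largest n (216 per arm), is not sought after withdrawal, although it is routine for those who remain in care here.

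The consequence is a risk of some avoidable bias in that one comparison. Its size cannot be derived from the protocol. The range of 8.2 to 10.6 points against the planned 10.0 only illustrates it, and depends on the assumed withdrawal share, 40% viraemia and imbalance between arms. Power is not a reason to act (96.6% against at most 98.4% at 300 per arm), and the named primary outcome is unaffected. The change is worth making because it is cheap and cannot be made in retrospect.

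**What to change.** In section 5.5, and in the consent form if it does not already allow this, add to the permission asked at withdrawal: use of routine month-12 and month-24 VL results and the date of any switch to second-line therapy, taken from the clinic record without contacting the patient. State that a month-24 VL obtained this way counts in the arm as randomised.

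The cost is an ethics amendment and a small record look-up: about 11 to 23 patients per arm under the assumed withdrawal share. No visit, sample or contact is added, and clinical management does not change. Some patients will decline or move their care elsewhere, and some routine VL dates may fall slightly outside the visit window.

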### 5.6 Replacement of individual subjects after withdrawal

Participants who withdraw from the study during the recruitment phase will be replaced until the intended numbers of inclusion at randomization (n=600) have been achieved.

Table 3: Overview of ITREMA study visits – Clinical procedures and Questionnaire data collection (standard of care arm and intervention arm)

|                                                                                                                                                                                                                                                                                                                                                                                                                                                                                                                                                                | Screening | Baseline | Month 3 | Month 6 | Month 7     |             | Month 9 | Month 12 | Month 15 | Month 18 | Month 21 | Month 24 | Control Arm Follow-up |                  | Intervention arm follow-up |                       |                       |               |
|----------------------------------------------------------------------------------------------------------------------------------------------------------------------------------------------------------------------------------------------------------------------------------------------------------------------------------------------------------------------------------------------------------------------------------------------------------------------------------------------------------------------------------------------------------------|-----------|----------|---------|---------|-------------|-------------|---------|----------|----------|----------|----------|----------|-----------------------|------------------|----------------------------|-----------------------|-----------------------|---------------|
| Clinical procedures                                                                                                                                                                                                                                                                                                                                                                                                                                                                                                                                            |           |          |         |         | If VL <1000 | If VL >1000 |         |          |          |          |          |          | If single VL>1000     | If twice VL>1000 | If single VL>1000          | If twice VL>1000; DL+ | If twice VL>1000; DL- | If resistance |
| Informed Consent & Eligibility Check                                                                                                                                                                                                                                                                                                                                                                                                                                                                                                                           | X         |          |         |         |             |             |         |          |          |          |          |          |                       |                  |                            |                       |                       |               |
| Randomization                                                                                                                                                                                                                                                                                                                                                                                                                                                                                                                                                  |           |          |         |         | X           |             |         |          |          |          |          |          |                       |                  |                            |                       |                       |               |
| Exclusion                                                                                                                                                                                                                                                                                                                                                                                                                                                                                                                                                      |           |          |         |         |             | X           |         |          |          |          |          |          |                       |                  |                            |                       |                       |               |
| Medical History                                                                                                                                                                                                                                                                                                                                                                                                                                                                                                                                                |           | X        |         |         |             |             |         |          |          |          |          |          |                       |                  |                            |                       |                       |               |
| Physical Exam/Vital Signs                                                                                                                                                                                                                                                                                                                                                                                                                                                                                                                                      |           | X        |         |         |             |             |         |          |          |          |          |          |                       |                  |                            |                       |                       |               |
| PE if symptomatic                                                                                                                                                                                                                                                                                                                                                                                                                                                                                                                                              |           |          | X       | X       | X           | X           | X       | X        | X        | X        | X        | X        | X                     | X                | X                          | X                     | X                     | X             |
| Clinical Outcomes                                                                                                                                                                                                                                                                                                                                                                                                                                                                                                                                              |           | X        |         |         |             |             |         |          |          |          |          |          |                       |                  |                            |                       |                       |               |
| Concomitant Medications                                                                                                                                                                                                                                                                                                                                                                                                                                                                                                                                        |           | X        |         |         |             |             |         |          |          |          |          |          |                       |                  |                            |                       |                       |               |
| Switch to second-line ART                                                                                                                                                                                                                                                                                                                                                                                                                                                                                                                                      |           |          |         |         |             |             |         |          |          |          |          |          |                       | X                |                            |                       |                       | X             |
| TDM-based counselling                                                                                                                                                                                                                                                                                                                                                                                                                                                                                                                                          |           |          |         |         |             |             |         |          |          |          |          |          |                       |                  | X                          |                       | X                     |               |
| Health care worker (P=physician, N=nurse, C=counselor)                                                                                                                                                                                                                                                                                                                                                                                                                                                                                                         | P/N/C     | P+N      | N       | N       | N           | P           | N       | N        | N        | N        | N        | N        | N                     | P+N              | N                          | P+N                   | P+N                   | P             |
| Questionnaire data                                                                                                                                                                                                                                                                                                                                                                                                                                                                                                                                             |           |          |         |         |             |             |         |          |          |          |          |          |                       |                  |                            |                       |                       |               |
| transmission/adherence factors, SES                                                                                                                                                                                                                                                                                                                                                                                                                                                                                                                            |           | X        |         |         |             |             |         |          |          |          |          | X        |                       |                  |                            |                       |                       |               |
| Health, QoL, self reported adherence                                                                                                                                                                                                                                                                                                                                                                                                                                                                                                                           |           | X        | X       | X       |             |             | X       | X        | X        | X        | X        | X        |                       |                  |                            |                       |                       |               |
| Legend: IA : Intervention arm, CA : Control arm. CD4 : CD4+ T-lymphocyte count. DBS : Dried blood spot. DL- : subtherapeutic drug level. DL+ : therapeutic drug level. EDTA : Ethylenediaminetetraacetic acid-containing vacutainer tube. FBC : Full blood count. PE : Physical exam. QoL : Quality of life. SES : Social-economic status. SSI : Sodium-separating vacutainer tube. TDM : Therapeutic drug monitoring. VL : Viral load determination. |           |          |         |         |             |             |         |          |          |          |          |          |                       |                  |                            |                       |                       |               |

Table 4: Overview of ITREMA study visits – Laboratory procedures and Blood draws (standard of care arm and intervention arm)

|                                                                                                                                                                                                                                                                                                                                                                                                                                                                                                                                                                | Baseline | Month 3 | Month 6 | Month 7     |             | Month 9 | Month 12 | Month 15 | Month 18 | Month 21 | Month 24 | Control arm follow-up of viremia |                  | Intervention arm follow-up of viremia |                       |                       |               |
|----------------------------------------------------------------------------------------------------------------------------------------------------------------------------------------------------------------------------------------------------------------------------------------------------------------------------------------------------------------------------------------------------------------------------------------------------------------------------------------------------------------------------------------------------------------|----------|---------|---------|-------------|-------------|---------|----------|----------|----------|----------|----------|----------------------------------|------------------|---------------------------------------|-----------------------|-----------------------|---------------|
| Laboratory procedures                                                                                                                                                                                                                                                                                                                                                                                                                                                                                                                                          |          |         |         | If VL <1000 | If VL >1000 |         |          |          |          |          |          | If single VL>1000                | If twice VL>1000 | If single VL>1000                     | If twice VL>1000; DL+ | If twice VL>1000; DL- | If resistance |
| Viral Load (CA = Control Arm, IA = Intervention Arm)                                                                                                                                                                                                                                                                                                                                                                                                                                                                                                           |          |         | CA+IA   |             |             | IA      | CA+IA    | IA       | IA       | IA       | CA+IA    | CA                               |                  | IA                                    |                       |                       |               |
| CD4                                                                                                                                                                                                                                                                                                                                                                                                                                                                                                                                                            |          |         | X       |             |             |         | X        |          |          |          | X        |                                  |                  |                                       |                       |                       |               |
| DBS and plasma storage (1 EDTA 9ml)                                                                                                                                                                                                                                                                                                                                                                                                                                                                                                                            | X        | X       | X       |             |             | X       | X        | X        | X        | X        | X        | X                                | X                | X                                     | X                     | X                     | X             |
| PBMC isolation (2 EDTA 9ml)                                                                                                                                                                                                                                                                                                                                                                                                                                                                                                                                    | X        |         |         |             |             |         |          |          |          |          |          |                                  |                  |                                       |                       |                       |               |
| therapeutic drug monitoring (TDM)                                                                                                                                                                                                                                                                                                                                                                                                                                                                                                                              |          |         |         |             |             |         |          |          |          |          |          |                                  |                  | X                                     |                       |                       |               |
| DBS-based resistance testing                                                                                                                                                                                                                                                                                                                                                                                                                                                                                                                                   |          |         |         |             |             |         |          |          |          |          |          |                                  |                  |                                       | X                     |                       |               |
| Other standard of care blood tests                                                                                                                                                                                                                                                                                                                                                                                                                                                                                                                             | X        | X       | X       |             |             |         | X        |          |          |          | X        | X                                | X                | X                                     | X                     |                       |               |
